### Statistical analysis

This is a within-group design with three measurement time points. We will investigate the proportion (percentage) of individuals that fulfill the above mentioned criteria at each given time point as estimates of prevalence of MCI and major neurocognitive impairment. Furthermore, we will conduct repeated-measures analysis of variance to investigate changes in cognitive performance over time, as well as the influence of different predictors. Cognitive performance of the individuals as a composite score and for each cognitive domain constitutes the dependent variables. The time of measurement and other control variables listed above represent the independent variables. A possible accumulation of the type I error is counteracted by an *α*-error correction (see below). The partial Eta-squared is calculated as the effect size, and the pairwise post-hoc comparisons are also corrected for multiple comparisons. The requirement of normal distribution is evaluated by the Kolmogorov–Smirnov test. Variance homogeneity is checked by Levene’s test. If the prerequisites for parametric statistics are not fulfilled, a distribution assumption-free covariance analysis according to the Quade model with rank-transformed variables is performed as an alternative.

Further questions are evaluated in terms of exploratory data analysis. Group differences are assessed using the t-test for independent samples or the Mann–Whitney-*U* test, depending on the scale level. Panels with discrete characteristics are analyzed with the *χ*^2^-test. Measures of correlation for discrete variables represent the contingency coefficients. For continuous characteristics, correlation measures according to Pearson (product-moment correlation) or Spearman (rank correlation) are used depending on the data level, in exceptional cases also according to Kendall (rank correlation without equidistance assumption).

The global significance level is set at *α* = 0.05. A false discovery rate (FDR) is calculated for *α*-error correction in multiple comparisons [35]. In the stepwise procedure, p-values are ranked in descending order; the null hypothesis is rejected if:1$$p(i) \le \frac{i}{m}\alpha$$ where *m* represents the number of *p* values and *i* the rank of the *p* value. Assuming *i* = 1, the FDR is equivalent to the Bonferroni correction.

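### The rank-based fallback (Quade's analysis of covariance) compares independent groups, so it cannot stand in for the repeated-measures ANOVA of within-patient change

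*Protocol article*

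**What the plan says.** The Statistical analysis section of the protocol article describes the design in one sentence: "This is a within-group design with three measurement time points". For the main analysis, "we will conduct repeated-measures analysis of variance to investigate changes in cognitive performance over time, as well as the influence of different predictors". The model terms are given next: "The time of measurement and other control variables listed above represent the independent variables".

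Two checks decide whether this analysis is used: "The requirement of normal distribution is evaluated by the Kolmogorov–Smirnov test", and "Variance homogeneity is checked by Levene’s test". If the prerequisites are not met, "a distribution assumption-free covariance analysis according to the Quade model with rank-transformed variables is performed as an alternative". The section names neither the grouping factor nor the covariate for that fallback.

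The Primary outcome measure section makes within-patient change primary in both parts: before against after transplantation in Part A, and the course over 12 months in already transplanted patients in Part B. The Sample size calculation section sizes the study for a within-person effect of f = 0.20 with 3 time points and 2 groups. It states N = 42 for 80% power and aims for 50 at follow-up.

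**The concern.** The reference to a covariance analysis on ranks identifies Quade's rank analysis of covariance, not his separate test for complete blocks. That method ranks outcome and covariate, takes residuals from the rank regression, and compares the residuals between groups by one-way ANOVA. It has no patient term and assumes that the groups are independent. The analysis it is meant to replace has one patient contributing all three values.

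The design's main statistical advantage is that each patient is their own control. A fallback that drops this could lead the study to report no change after transplantation only because an assumption check failed.

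A smaller matter concerns the checks. Levene's test compares variances between independent groups. It suits a Part A versus Part B factor, but it says nothing about sphericity (equal variances of the within-patient differences), on which the F-test for time depends. Visits fall at baseline, 3 and 12 months, and in Part A surgery lies between the first two, so equal correlations cannot be taken for granted.

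**Working it through.** **Inputs from the article.** Three visits, two groups, f = 0.20, power 0.80, stated N = 42, target 50 (Sample size calculation); α = 0.05 (Statistical analysis). The visit correlation ρ and the sphericity parameter ε are not given and are assumed below.

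**1. The plan's own figure.** For the within-person effect, λ = f²·N·m·ε/(1−ρ), df1 = (m−1)ε, df2 = (N−k)(m−1)ε. With ρ = 0.5 and ε = 1:
- λ = 0.04 × 42 × 3 / 0.5 = 10.08, df1 = 2, df2 = 40 × 2 = 80, power 0.803.
- At N = 40, power is 0.782.

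So N = 42 reproduces exactly, with ρ = 0.5 and ε = 1 as unstated inputs. Other correlations at ε = 1 give other sizes (ρ = 0.3: 58; ρ = 0.7: 26).

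**2. What ignoring the pairing costs.** With equal variances σ², the difference between two visit means has variance 2σ²(1−ρ)/n. An independent-groups analysis uses 2σ²/n, which is too large by the factor 1/(1−ρ): 2 at ρ = 0.5 and 3.3 at ρ = 0.7. The test statistic shrinks accordingly, so the error is conservative.

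**3. Simulation.** Normal data with unit variance and equal correlation 0.5; means −0.245, 0, 0.245, whose standard deviation is √[(0.06 + 0 + 0.06)/3] = 0.20 = f. Quade is run with visits as groups and no informative covariate.

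| n | RM-ANOVA power | Friedman power | Quade power | Quade type I error |
|---|---|---|---|---|
| 25 | 0.55 | 0.43 | 0.19-0.20 | about 0.5% |
| 50 | 0.86-0.88 | 0.72-0.74 | about 0.53 | about 0.5% |

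The n = 25 row assumes an even split of the 50 between the parts, which the article does not state.

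**4. Effect of a covariate (n = 50, ρ = 0.5).** Quade's power rises to about 0.60 with a weak covariate, 0.69 with one correlated 0.7 with patient level, and 0.78 at correlation 0.9. Friedman stays near 0.74.

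**5. Higher visit correlation.** At ρ = 0.7, N = 42 and a weak covariate, power is 0.48 for Quade, 0.96 for repeated-measures ANOVA and 0.89 for Friedman. Quade's type I error is 0.05%.

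**6. The other reading.** Suppose Quade compares Part A with Part B at follow-up, with baseline as covariate. The groups are then independent and the method is valid. It tests a difference between parts, however, and not change over time within either part.

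**7. Sphericity.** The uncorrected F-test at n = 50 was simulated under assumed correlations (0-3, 0-12, 3-12 months):
- 0.5/0.5/0.8: ε = 0.80, type I error 6.0%.
- 0.8/0.4/0.5: ε = 0.77, 6.1%.
- 0.6/0.5/0.9: ε = 0.66, 6.7-7.0%.

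With an ε correction, the formula in step 1 gives at N = 42 and ε = 0.75: λ = 7.56, df1 = 1.5, df2 = 60, power 0.714. At N = 50 and ε = 0.80, power is 0.812.

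**The case against.** The article never says that the visits would be Quade's groups. It plans predictors and control variables and assumes two groups in the sample size, so a between-group use with baseline as covariate is a fair reading. This stands, and it is why the point is put as two alternatives. It does not rescue the fallback, because that reading leaves the primary within-patient questions without a rank test.

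A reader might infer that the fallback is likely to be used, since neuropsychological scores can have floors and ceilings. The document gives no score distributions, and the outcomes are norm-adjusted z-scores analysed as a composite and by domain. In a simulation at n = 50, a standard Kolmogorov-Smirnov test with estimated mean and SD rejected mildly skewed data only 1.2-1.8% of the time. A corrected version of the test, or stronger skew, would reject more often. The frequency is unknown.

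A reader might also infer that the primary test would lose most of its power. That holds only at the assumed n = 25. At the target of 50 the loss is about two-fifths, (0.87 − 0.53)/0.87 = 39%, and a strong covariate recovers much of it. The simulations also use normal data, under which the fallback would not normally be called, so they show the cost of dropping the pairing and do not predict this trial's power.

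Finally, a condensed article may leave Mauchly's test or an ε correction to the full plan, and this one does not say that the F-test is uncorrected. Levene's test is proper for a two-group factor. Sphericity is therefore a secondary note.

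**Conclusion.** The point holds, and the fallback is wrong as written. The article itself names the method that replaces the repeated-measures ANOVA, and under neither reading does that method do the job: with visits as groups it ignores the pairing, and with Part A and Part B as groups it does not test change over time.

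On the first reading, the size at n = 50 is power of about 0.53 against 0.86-0.88 for the planned analysis, with type I error of about 0.5% at a nominal 5%. This rests on f = 0.20, an assumed visit correlation of 0.5, normal data and no informative covariate. The error costs power and does not create false positives.

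The sphericity note is lesser: type I error of about 6-7% if no correction is applied, at assumed ε of 0.66-0.80. A reader might conclude that the stated N = 42 is miscalculated. It is not: it reproduces exactly, but with ε = 1 among its unstated inputs.

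**What to change.** For the time effect, replace Quade with a method that respects pairing. Where no group or covariate is needed, use Friedman's test with paired Wilcoxon comparisons within each part, under the false discovery rate correction already planned. Friedman and Wilcoxon cannot carry the two groups or the control variables. Where those are needed, keep the planned model and take confidence intervals from a bootstrap that resamples whole patients. Keep Quade only for between-group comparisons, and name its groups and covariate.

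In the same paragraph, state that the time effect is tested with a Greenhouse-Geisser correction, or use a mixed model with unstructured visit covariance, which does not need sphericity. Levene's test can stay for the between-group factor. Give the correlation and ε behind N = 42.

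The cost is a few sentences of analysis wording, settled before the data are analysed, and standard software. No change to data collection or visits is needed.

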#### The cognitive test battery

We first administer the Mini-Mental Status Examination (MMSE) [17] as a neurocognitive screening test, together with a test battery consisting of five tests, assessing the cognitive domains of selective attention, verbal and visual memory with short-delay and long-delay memory conditions, verbal working memory, word fluency and symbol processing. Raw scores are transformed into z-scores adjusted for age, and if available sex, as well as years of education.

The individual’s degree of impairment will be stratified using the algorithm adopted by Murray and colleagues [1] based on the Mayo criteria for mild cognitive impairment (MCI) [18] and the Diagnostic and Statistical Manual, fifth Edition, criteria for major neurocognitive impairment as approximate guidelines [19].

Individuals will be classified depending on their extent of impairment and the number of affected domains as.Unimpaired: performance better than 1.5 standard deviations (SD) below the norm sample in any test considered for the classification.Mildly impaired: mild deficits (scores 1.50 to 1.99 SD below the norm sample) in only one domain.moderately impaired: deficits in two domains or a severe deficit (2.0 SD below the norm Sample) in one domain.Severely impaired: deficits in at least two domains.

The domains of executive functions (semantic and phonemic fluency, working memory, and mental flexibility), verbal memory (immediate and delayed recall, recognition), visual memory (delayed recall), and attention (symbol processing speed) are considered in the classification.

For this purpose, we will use the following validated tests (Table 2):

**Table 2 Tab2:** The different neurocognitive tests and their affiliation to a particular cognitive domain

Cognitive domain	Test
Visual memory	ROCFT
Verbal memory	VLMT
Attention	TMT A WMS-R–numbers forward
Executive function	TMT B WMS-R–numbers backwards RWT

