### Patient baseline data, comorbidity, laboratory parameters

In addition, baseline patient data, such as age, type of underlying disease, type and duration as well as the dose (*Kt/V*) of the dialysis therapy will be obtained. Comorbidities, that may have an impact on cognitive performance (such as previous stroke, coronary heart disease, hypertension diabetes mellitus, existing dementia or depression), will be documented. Furthermore, blood parameters such as hemoglobin, creatinine, calcium, phosphorus, albumin, triglycerides, cholesterine, urea, pH-value, CO_2_, and bicarbonate will be recorded. Current medication data will be obtained from the medical records and by self-report at each testing session. In addition, changes in medication are recorded. The examinations,were executed by trained and certified medical students.

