### Secondary outcome measures

As a secondary outcome, we will assess a distinct profile of cognitive function using standard neurocognitive tests. Furthermore, we will explore the impact and temporal development of a set of risk factors for deficits in cognitive performance. Second, we want to examine the extent to which cognitive impairment affects depression at all follow-up time points. Third, we want to assess how stressors negatively or positively affect cognitive performance. Fourth, we want to investigate to what degree cognitive performance affects the formation and development of donor-specific antibodies.

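### The contingency coefficient fixed for discrete variables in the exploratory analyses depends on table size and ignores the order of the impairment classes, so its values do not compare as strengths of association (minor)

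*Protocol article*

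**What the plan says.** The relevant wording is in the protocol article, section Statistical analysis, in the paragraph that opens "Further questions are evaluated in terms of exploratory data analysis". Discrete data get a test ("Panels with discrete characteristics are analyzed with the" chi-squared test) and a measure of strength: "Measures of correlation for discrete variables represent the contingency coefficients". The term is plural and generic, and no formula, variant or correction is given. For continuous data the same paragraph chooses between Pearson, Spearman and Kendall by data level. For discrete data it does not separate ordered from unordered variables.

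Three other sections show where such a measure would be used:

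- **Secondary outcome measures:** "we will explore the impact and temporal development of a set of risk factors for deficits in cognitive performance".
- **The cognitive test battery:** "Individuals will be classified depending on their extent of impairment and the number of affected domains". The result is four ordered classes, from unimpaired to severely impaired.
- **Patient baseline data, comorbidity, laboratory parameters:** present/absent conditions ("previous stroke, coronary heart disease, hypertension diabetes mellitus, existing dementia or depression") stand beside factors that can have several categories, such as "type of underlying disease" and type of dialysis.

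**The concern.** A measure of association is reported so that its size can be read as strength. Pearson's C does not serve that purpose across tables of different shape. At sample sizes of 50 to 100, much of its value in a larger table is sampling noise that grows with the number of cells. A factor with several categories can therefore show a larger C than a binary comorbidity even when only the comorbidity is related to cognition.

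Two further properties matter because the natural discrete outcome is an ordered class. C gives the same value whichever way the classes are arranged, so it discards their order. It is also never negative, so it cannot show whether a factor goes with better or worse classes.

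What is at stake is the reported strength and direction of association in an exploratory secondary aim.

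**Working it through.** **The plan's own figures.** The article gives no number for this coefficient. Its one reproducible figure, the sample size of 42, gives power 0.803 if the correlation between repeated measures is 0.5 and sphericity holds (both assumed). Nothing below depends on it.

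**Inputs from the article.** n = 100 (Abstract, cohort size); n = 50 (Sample size calculation, follow-up target); four impairment classes; two levels per comorbidity.

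**Assumed inputs.** The number of categories for underlying disease is not stated; 3 to 6 is assumed. Margins are taken as uniform unless noted.

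**Step 1: ceiling.** C = √(χ²/(χ²+n)). Its maximum is √((k−1)/k), where k is the smaller table dimension: √(1/2) = 0.707 for k = 2, √(2/3) = 0.816 for k = 3, √(3/4) = 0.866 for k = 4. Extra factor categories raise the ceiling only while the factor has fewer levels than the outcome. If the outcome is collapsed to two classes, the ceiling is 0.707 for every factor.

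**Step 2: expected sample value with no association.** χ² then averages about (r−1)(c−1), so C is roughly √(df/(df+n)). At n = 100 this is √(3/103) = 0.17 for 2×4 and √(15/115) = 0.36 for 6×4. Simulation (40,000 tables per setting) gives:

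| Table | Mean C, n = 50 | Mean C, n = 100 | Mean bias-corrected V, n = 50 | Mean bias-corrected V, n = 100 |
|---|---|---|---|---|
| 2×2 | 0.111 | 0.079 | 0.050 | 0.034 |
| 2×4 | 0.221 | 0.157 | 0.078 | 0.054 |
| 3×4 | 0.316 | 0.229 | 0.070 | 0.049 |
| 4×4 | 0.382 | 0.280 | 0.065 | 0.045 |
| 6×4 | 0.475 | 0.356 | 0.073 | 0.052 |

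Bias-corrected V is √(φ²/(min(r*, c*)−1)), with φ² = max(0, χ²/n − (r−1)(c−1)/(n−1)), r* = r − (r−1)²/(n−1), and c* likewise. It is nearly flat across the tables with four outcome classes.

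Two simpler repairs fall short. At n = 100, going from 2×4 to 6×4, dividing C by its ceiling still leaves a rise from 0.222 to 0.411. Plain Cramer's V still rises from 0.160 to 0.221. Collapsing the outcome to two classes does not help either: mean null C goes from 0.079 (two-level factor) to 0.208 (six-level factor).

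**Step 3: what one value of C means.** At n = 100 the 5% critical value of χ² corresponds to C = 0.269 in a 2×4 table and 0.447 in a 6×4 table. An observed C of 0.35 is thus clear evidence of association in the first, and slightly below the no-association average (0.356) in the second.

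**Step 4: illustration of misordering, on assumed effects.** An unrelated six-level factor shows a larger C than a binary factor with a true effect of w = 0.3 in 68% of samples at n = 100 and 89% at n = 50. In another scenario (class shares 40/20/25/15%, a 30/70 binary factor, an unrelated five-category factor), repeat simulations give:

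| Latent shift | n | C | Bias-corrected V |
|---|---|---|---|
| 0.5 SD | 50 | 88–89% | 21–22% |
| 0.8 SD | 50 | 72–73% | 10–11% |
| 0.5 SD | 100 | 76–77% | 13–14% |
| 0.8 SD | 100 | 41–43% | 2–3% |

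The 6×4 table is sparse: 50/24 ≈ 2 and 100/24 ≈ 4 expected per cell.

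**The case against.** The strongest reply is that the property of C is real but the plan does not use C in a way that does harm. Most of that reply stands.

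- **No ranking is planned.** A reader might infer that risk factors will be ordered by C. The article says only that their impact will be explored. Predictors of the cognitive scores go to another method: "we will conduct repeated-measures analysis of variance to investigate changes in cognitive performance over time, as well as the influence of different predictors", with partial eta-squared as effect size.
- **The cross-table is not spelled out.** The classes are explicitly used for proportions at each time point. Tabulating them against risk factors is a natural use of the discrete-variable sentence, but not a stated one.
- **Significance is not inflated.** A reader might infer that many-category factors will turn up falsely significant. The chi-squared reference distribution allows for the degrees of freedom, and false discovery rate control is also stated.
- **Order is not ignored everywhere.** The Mann–Whitney test is listed for group differences according to scale level, which can cover a binary comorbidity against the ordered class. Direction can also be read from the cross-table itself.
- **Many tables have equal size.** The listed comorbidities are naturally present/absent, so against one outcome their C values do compare.
- **The term may include Cramer's V.** It may. Plain V reduces the problem without removing it: in the second scenario of step 4 the misordering is 43% and 21% at n = 50, and 26% and 4% at n = 100.

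What remains is that the tests are protected but the reported strength is not. The ANOVA of continuous scores gives no measure for the impairment classes. The sentence is a stated choice of method, so replacing it is more than filling in detail left to a fuller plan.

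**Conclusion.** The point holds as a minor weakness of the exploratory analyses. With 50 to 100 patients, Pearson's C from tables of different size cannot be compared as strength of association, and for the ordered impairment class it loses both order and sign. The firm part is algebraic: the expected null value depends on (r−1)(c−1)/n, and the ceiling depends on the smaller dimension. The population value under no association is 0 for every table, so the inflation is a finite-sample effect.

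The misordering percentages show what can happen under assumed category counts, margins and effect sizes, none of which the article gives. They are not a forecast for this study, and they shrink with larger n and stronger effects. It would be wrong to conclude that the primary outcome, the sample size, the ANOVA results or the error rate is compromised; none of them uses this coefficient.

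**What to change.** Replace the sentence on contingency coefficients in Statistical analysis with wording to this effect:

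- Associations of the impairment class with binary or ordered factors are given as Kendall's tau-b with a 95% CI.
- Associations with unordered factors of more than two categories are given as bias-corrected Cramer's V with a CI.

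A proportional-odds model, giving an odds ratio for a worse class, is optional. It adds an assumption that four classes in 50 to 100 patients can check only weakly.

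The new text should also say that tau-b and V are on different scales and are not to be compared with each other. If factors of both kinds are ever set side by side, bias-corrected V should be used for all of them, as in the comparison in step 4. Tau-b is signed and centred on 0 under no association, but it cannot reach 1 in a 2×4 table. With equal groups and equal classes its maximum is (1/4)/√((1/4)(3/8)) = 0.816.

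The cost is a small change of wording and no new data. The downside is that the reported association figures become smaller.

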### Sample size calculation

In order to investigate the prevalence of MCI or dementia, all individuals currently registered on the local transplant list, who are able to consent and agree to participate in the study, will be included. Currently, this list includes 142 individuals (75 individuals are in status T (transplantable), 67 individuals are in status NT (non-transplantable).

With regard to outcome measures, previous studies have shown highly significant improvements in some domains after transplantation [36], but have not reported effect sizes or statistical parameters that could be used to calculate effect sizes. Harciarek and colleagues [37, 38] report moderate to strong “time × comparison with healthy controls” interaction effects. We therefore conservatively expect to find low to medium effect sizes. For the detection of low to medium (*f* = 0.20) within-person effects with 3 measurement time points and 2 groups using a repeated-measures ANOVA as explained above, a power (1 – *β* (type II error probability) of 0.80 and a type-I error probability (*α*) of 0.05, a sample size of 42 is necessary [39, 40]. We therefore aim for a sample size of 50 persons for the follow-up measurements.

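### The false-discovery-rate rule ranks p-values in descending order, which reverses its thresholds and contradicts its own Bonferroni remark; as written it is not a valid FDR procedure.

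*Protocol article*

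**What the plan says.** The Statistical analysis section of the protocol article names several dependent variables: "Cognitive performance of the individuals as a composite score and for each cognitive domain constitutes the dependent variables". Table 2 lists four domains. The section also plans corrected pairwise post-hoc comparisons, and for control of the type I error it points forward to a correction described at its end.

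That correction is the only one named. The level is given first: "The global significance level is set at *α* = 0.05". The method follows: "A false discovery rate (FDR) is calculated for" the α-error correction in multiple comparisons, with a literature reference. Then comes the decision rule: "In the stepwise procedure, p-values are ranked in descending order; the null hypothesis is rejected if" p(i) ≤ (i/m)α, where m "represents the number of *p* values and *i* the rank of the *p* value". The section closes by saying that, at i = 1, "the FDR is equivalent to the Bonferroni correction".

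**The concern.** Three elements fix the rule: the direction of the ranking, the definition of i as the rank, and the threshold (i/m)α. With descending ranks, rank 1 is the largest p-value and rank m the smallest. The threshold grows with i, so the strictest limit falls on the weakest result, and the strongest result is tested at (m/m) × 0.05 = 0.05, that is, with no correction. A valid FDR step-up rule does the opposite.

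The closing remark points the other way. A Bonferroni limit at i = 1 protects against false positives only if rank 1 is the smallest p-value. An analyst cannot apply the stated ordering and keep the sense of that remark.

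Cognitive performance is the primary outcome for both parts of the study, so the rule bears on the main results as well as on side questions.

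**Working it through.** **Inputs.** From the Statistical analysis section: α = 0.05, the threshold (i/m)α, and i as the rank in descending order. The article gives no number for m. The values used here are assumptions: 3 (pairwise comparisons of three time points), 5 (composite plus four domains), 10 (illustrative) and 15 (5 outcomes × 3 pairs). Correlations between tests are also assumed.

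**Step 1: thresholds for m = 5.**

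| p-value | ascending ranks | descending ranks (as written) |
|---|---|---|
| smallest | 0.01 | 0.05 |
| 2nd smallest | 0.02 | 0.04 |
| 3rd smallest | 0.03 | 0.03 |
| 4th smallest | 0.04 | 0.02 |
| largest | 0.05 | 0.01 |

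**Step 2: does the proper rule meet the stated 0.05?** With ascending ranks, all nulls true and independent tests, 200,000 simulated runs gave a false-rejection probability of 0.050 (m = 3), 0.051 (m = 5) and 0.050 (m = 15). For m = 5 with equally correlated tests, a separate simulation gave 0.045 at correlation 0.5 and 0.040 at 0.7. The stated level is met, within simulation error.

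**Step 3: the written rule, each p-value against its own threshold.** No threshold exceeds α, and the smallest p-value faces α itself. So something is rejected exactly when the smallest p-value is at most 0.05. With all nulls true and independent tests, the probability is 1 − 0.95^m:

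- m = 3: 1 − 0.857 = 0.143
- m = 5: 1 − 0.774 = 0.226
- m = 10: 1 − 0.599 = 0.401
- m = 15: 1 − 0.463 = 0.537

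Simulation gave 0.143, 0.228 and 0.537 for m = 3, 5 and 15. For m = 5 with correlated tests it gave 0.182 at correlation 0.5 and 0.149 at 0.7.

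**Step 4: two examples, m = 5.**

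- p = 0.045, 0.2, 0.4, 0.6, 0.8. Ascending: 0.045 > 0.01 and every other value exceeds its limit, so nothing is rejected. As written: 0.045 ≤ 0.05, so it is rejected.
- p = 0.001, 0.012, 0.028, 0.039, 0.2. Ascending: the first four meet 0.01, 0.02, 0.03 and 0.04, so four are rejected. As written: 0.039 faces 0.02 and fails, so only three are rejected.

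The written rule therefore errs in both directions.

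**Step 5: other ways to run the descending rule.**

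- Start at i = 1 and stop at the first failure: nothing can be rejected unless the largest p-value is at most α/m. For five independent true nulls that probability is 0.01^5 = 10^-10. With one or two real effects among five (z-shift 2.8, independent tests), simulated power was 0.000.
- Start at i = m and stop at the first failure: with all nulls true, the same false-rejection probabilities as in step 3.
- Find the largest i that meets the inequality and reject ranks 1 to i: a smallest p-value of at most 0.05 then rejects every hypothesis. With one real effect among five, the simulated FDR was 0.67, against 0.04 for the ascending rule.

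**Step 6: real effects under the step 3 reading.** With m = 5 and independent tests, the simulated FDR was 0.10 with one real effect (0.04 ascending) and 0.046 with two (0.029 ascending). The excess is largest when few effects are real.

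**The case against.** The strongest reply is that most of the section points to the standard rule. It names the FDR, cites a source, prints the usual threshold and adds the Bonferroni remark. One word is out of line, and it has an innocent explanation: a step-up search may properly begin at the largest p-value, provided the ranks are still numbered from the smallest. Standard software may well apply the right rule whatever the text says. This stands as an account of what was probably meant. It does not repair the text, which defines i as the rank immediately after calling the ranking descending.

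A second reply is that the loss of error control is not certain. This also stands. The section calls the procedure stepwise without giving the steps. Of the four ways of running the descending rule that were simulated, three exceed 5% when all nulls are true, and one rejects almost nothing.

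A third is that independence overstates the inflation, because a composite and its domains come from the same patients. That is right, and the independent-test figures are upper ends. Positive correlation reduces the excess without removing it at the values examined.

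A reader might also infer that the article is deficient because it neither spells out the step-up clause nor defines the family or a single primary test. The documents do not support that as part of this point. A condensed article may leave such details to the full protocol or analysis plan, and family definition is a separate matter from the ranking direction.

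**Conclusion.** The point holds in this form: the decision rule as written reverses the FDR thresholds, contradicts the Bonferroni remark beside it, and is not a valid FDR procedure. It is probably a slip of wording. It still needs correcting, because it sits in the only multiplicity correction named for the primary cognitive outcomes.

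If each p-value is compared with its own threshold and all nulls are true, the chance of a false rejection is 14%, 23% and 40% for assumed m = 3, 5 and 10 with independent tests, and about 15% to 18% for m = 5 at assumed correlations of 0.7 to 0.5. The proper rule gives at most 5%. These sizes rest on an m that the article does not state, on assumed correlations and on that one way of running the rule.

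A reader might go further and conclude that the study has deliberately chosen an uncorrected analysis, or that error control is lost whichever way the rule is run. Neither follows: the Bonferroni remark points to the standard procedure as the intention, and one sequential reading is extremely conservative. The sample size is not affected. The statement that "a sample size of 42 is necessary" rests on a single repeated-measures ANOVA at α = 0.05 and does not use the FDR rule.

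**What to change.** In the Statistical analysis section, change *descending* to *ascending* and state the rule in full, for example: the p-values are ranked in ascending order, p(1) ≤ … ≤ p(m); let k be the largest i with p(i) ≤ (i/m)α; hypotheses 1 to k are rejected, and none if no such i exists. The Bonferroni remark can stay if it says that the limit for the smallest p-value, i = 1, equals the Bonferroni limit α/m.

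The cost is one sentence of analysis wording, best settled before the data are analysed. It needs no further patients, assessments or data, and the sample size stays as it is.
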